|-------------------|---------------------------|----------------------|----------------------------------------------------------------------------------------------------------------------------------------------------------------------------------------------------|-------------------------------------------------------------------------------------------------------------------------------------------------------------------------------------------------------------------------------------------------------------------------------------------------------------------------------------------------------------------------------------------------------------------------------------------------------------------------------------------------------------------------------------------------------------------------------------------------------------------------------------------------------------------------------------------------------------------------------------------------------------------------------------------------------------------------------------------------------------------------------|
| CR                |                           |                      |                                                                                                                                                                                                    |                                                                                                                                                                                                                                                                                                                                                                                                                                                                                                                                                                                                                                                                                                                                                                                                                                                                               |
| Mod32             | 6/11/19                   | 6/20/19              | 
 
1- Remove [name], add [name] and [name] as Key Study Personnel
 
2- Edits to patient qualitative interview guide
 
 | 
 
1- [name], Clinical Research Coordinator PT help for patient monitoring; [name], SUMR scholar working on alert analysis
 
2- The semi-structured interview guide questions/probes script has been edited to more accurately reflect the flow of conversation.
 
                                                                                                                                                                                                                                                                                                                                                                                                                                                                                                                                      |
| Mod33             | 8/9/19                    | 8/21/19              | 
 
1- [name] added and [name] removed as Key Study Personnel
 
2- Provider qualitative interview guides and protocol added
 
      | 
 
1- [name], Data Analyst for pulling PennChart patient outcome data; initiation of provider qualitative interviews
 
2- A qualitative component for providers is being added to the study to assess the impact of the CHF Empower program on providers' perceptions of how easy the program was to use, the program's impact on patient care, and the effect on patients' health.
 
                                                                                                                                                                                                                                                                                                                                                                                                                                 |
| Mod34 – Deviation | 1/13/20                   | 2/12/20              | [name] added and removed as Key Study Personnel                                                                                                                                             | Corrected omission of [name], Data Analyst for pulling PennChart outcome data. [name] had not been added (or subsequently removed) as Key Study Personnel in the IRB Protocol. [name] worked on the study starting in March of 2018 and stopped working on the study in August of 2019 when she left UPenn for another position. This omission of adding and removing [name] as Key Study Personnel was an oversight by the Project Director. [name] was tasked specifically with occasional (biannual) data pulls of hospital readmissions for the enrolled study participants. The data pulls necessarily involved the viewing and handling of data with PHI. [name] then securely transferred these data pulls to the study team in order for them to prepare summary reports for the Data and Safety Monitoring Board to assess study safety. |
| File Name  | Date of Submission | Approval date | Summary                                                                                                                                                                                     | Rationale                                                                                                                                                                                                                                                                                                                                                                                                                                                                                                                                                                                                                                                                                                                                                                                                                                                              |
| Mod35             | 2/13/20                   | 2/19/20              | Add [name] added and [name] removed as Key Study Personnel                                                                                                                            | [name], Data Director overseeing all study analyses                                                                                                                                                                                                                                                                                                                                                                                                                                                                                                                                                                                                                                                                                                                                                                                                                      |
| Mod36 –           | 3/10/20                   | 3/31/20              | Continuing Review                                                                                                                                                                                  | Annual Continuing Review                                                                                                                                                                                                                                                                                                                                                                                                                                                                                                                                                                                                                                                                                                                                                                                                                                                      |

Remote monitoring and behavioral economics in managing patients discharged from the hospital with heart failure: a randomized clinical trial

| CR        |                    |               |                                                                                                                                                                                                                           |                                                                                                                                                                                                                                                                                                                                                                                                                                                                                                                               |
|-----------|--------------------|---------------|---------------------------------------------------------------------------------------------------------------------------------------------------------------------------------------------------------------------------|-------------------------------------------------------------------------------------------------------------------------------------------------------------------------------------------------------------------------------------------------------------------------------------------------------------------------------------------------------------------------------------------------------------------------------------------------------------------------------------------------------------------------------|
| Mod37     | 4/1/20             | 4/2/20        | [name] added as Key Study Personnel                                                                                                                                                                                   | [name], Data Analyst for study outcomes                                                                                                                                                                                                                                                                                                                                                                                                                                                                                   |
| Mod38     | 4/22/20            | 4/24/20       | Amended secondary outcome variable to include "assess cause-specific rehospitalizations"                                                                                                                                  | A secondary endpoint will be cause-specific rehospitalization, the rationale being that evaluating cause-specific hospital admission will allow a more complete understanding of the potential effects of the intervention, by indicating how many of the readmissions are due to what cause (e.g., heart failure, MI, stroke, other cardiovascular cause, non-cardiovascular cause, etc).                                                                                                                                    |
| Mod39     | 5/14/20            | 5/18/20       | [name] added as Key Study Personnel                                                                                                                                                                                 | [name], Data Analyst for CareEverywhere outcome data                                                                                                                                                                                                                                                                                                                                                                                                                                                                    |
| Mod40     | 6/17/20            | 6/25/20       | 
1- [name] added as Key Study Personnel.
 
2- Change to Subject Confidentiality section in protocol to clarify how the NJDOH inpatient data will be matched to study participants
 
:
 
.
 | 
1- [name], Data Analyst for CareEverywhere outcome data
 
2- In Subject Confidentiality, the following has been added to clarify the process: For obtaining NJDOH state-based hospitalization data, NJDOH will send state-wide inpatient data from 2016-2020 with name, DOB, address, gender, race, and ethnicity. Our data analysts will match on these variables to the enrolled participants.
                                                                                                              |
| File Name | Date of Submission | Approval date | Summary                                                                                                                                                                                                                   | Rationale                                                                                                                                                                                                                                                                                                                                                                                                                                                                                                                     |
| Mod41     | 6/29/20            | 6/30/20       | Subject Confidentiality section of protocol updated to include review of CareEverywhere data                                                                                                                              | Participants in this study consent to having their medical care reviewed during the period they are enrolled in the study (365 days). This includes reviewing inpatient medical information contained in PennChart (all participants were Penn Med patients at the time of enrollment) as well as state-based inpatient data from NJ, DE and PA to capture re-hospitalizations that may have occurred outside of Penn Medicine. This modification is to clarify that we will also plan to review the CareEverywhere data that |

Remote monitoring and behavioral economics in managing patients discharged from the hospital with heart failure: a randomized clinical trial

|  |  |  |  |                                                                                                                                                                                                                                                                                                                                                                                                                                                                                                                                                            |
|--|--|--|--|------------------------------------------------------------------------------------------------------------------------------------------------------------------------------------------------------------------------------------------------------------------------------------------------------------------------------------------------------------------------------------------------------------------------------------------------------------------------------------------------------------------------------------------------------------|
|  |  |  |  | further details the clinical reasons for readmissions that occur outside Penn Medicine and is already a part of the enrolled participants’ PennChart medical record. The information contained in CareEverywhere (combined with the state based inpatient data) is crucial to assessing the main outcome of the study by ensuring we are accurately assessing the clinical reasons enrolled participants are being readmitted and that we are doing this assessment using the same procedures used to assess the readmissions that occur at Penn Medicine. |
|--|--|--|--|------------------------------------------------------------------------------------------------------------------------------------------------------------------------------------------------------------------------------------------------------------------------------------------------------------------------------------------------------------------------------------------------------------------------------------------------------------------------------------------------------------------------------------------------------------|

535

536

537

1538 Original Statistical Analysis Plan

1539 Statistical considerations

1540 Power and sample size issues. Our primary outcome is time to first readmission for any cause. The  
1541 primary comparison will be the time to event compared between the intervention arm and the usual  
1542 care arm; that is, the primary hypothesis is whether a series of interventions, adapted to the behavior  
1543 and outcomes of each particular patient, will reduce readmission rates compared to usual care.

1544 We expect the 1-year event rate to be 47% in the usual care arm based on data obtained on our target  
1545 population at UPHS. We wish to have 80% power to detect an absolute decrease in this rate of about  
1546 10% in the intervention group; this corresponds to a hazard ratio of 0.73. We will accrue 500 patients  
1547 over the 24-month enrollment period and follow them for an additional 12 months; with the 1:1  
1548 randomization ratio, we will have 250 control subjects and 250 intervention subjects. The primary  
1549 hypothesis will use a two-sided Type I error rate of 0.05.

1550 Data analysis plans

1551 Prior to analysis, we will produce data summaries including graphical methods to assess data quality,  
1552 examine central tendencies and distributional assumptions and randomization success. The primary  
1553 analysis will consist of unadjusted intent-to-treat hypothesis tests using the logrank test to compare the  
1554 time to hospitalization in the two groups. We will also estimate Cox proportional hazards regression  
1555 models adjusted for the stratification variable and other covariates of interest (such as patient sex,  
1556 income, race, baseline ejection fraction, and quality of life), retaining these given evidence of  
1557 confounding or predictive ability. We will employ a confounder selection method based on "change in  
1558 estimate" criterion. We will assess interaction terms between the a priori potential effect modifiers such  
1559 as income level, race, and baseline ejection fraction. All hypothesis tests will be two-sided and models  
1560 will be assessed using standard diagnostic techniques. We will use standard approaches to assess the  
1561 proportional hazards assumption and include interaction terms with time if necessary. We will also fit  
1562 frailty models to analyze repeated rehospitalizations within patients; these models properly adjust for  
1563 the correlation of multiple events within individuals.

1564 Handling of missing data is an important issue in all RCTs. Follow-up data may be missing if participants  
1565 miss the follow-up visit or withdraw. . Even in subjects who are lost to follow-up, however, we will be  
1566 able to capture any events that result in hospitalization, and thus will still be able to observe our primary  
1567 outcome. We will compare dropout rates by arm, will attempt to find the reasons for missing data and  
1568 will compare baseline characteristics in participants with complete vs. incomplete follow-up. In  
1569 secondary analyses we will investigate the sensitivity to modeling assumptions using imputation models  
1570 and inverse-probability-weighted estimating equations and models that adjust for informative missing  
1571 data.

1572 Cost effectiveness analysis

1573 To assess the cost-effectiveness of the interventions, we will use analytic methods for economic  
1574 evaluations in clinical trials. Our approach will be similar to Specific Aim 3 using cost as the outcome. We  
1575 will use generalized linear models to adjust for the stratification variable and other factors. Cost-  
1576 effectiveness ratios will be calculated as the difference in costs divided by the difference in  
1577 rehospitalization rate calculated under Specific Aim 3 for the "within-trial" analysis, with parametric 95%  
1578 CIs for the cost per percentage point increase in adherence and acceptability curves. Standard errors  
1579 and the correlation of the difference in cost and effect will be obtained using a bootstrap procedure. A

Remote monitoring and behavioral economics in managing patients discharged from the hospital with heart failure: a randomized clinical trial

further cost-effectiveness analysis from the “societal perspective” will be conducted to assess the impact of the rehospitalization rate reductions measured as cost per QALY gained. To address uncertainty in the micro simulation model, we will also conduct a probabilistic sensitivity analysis (PSA) by defining probability distributions for the variables in the model used to calculate costs and effectiveness. We will use the results of the PSA to calculate confidence (or credible) intervals and acceptability curves.

## Final Statistical Analysis Plan

### Statistical considerations

Power and sample size issues. Our primary outcome is time to readmission for any cause. The primary comparison will be the times to events compared between the intervention arm and the usual care arm; that is, the primary hypothesis is whether a series of interventions, adapted to the behavior and outcomes of each particular patient, will reduce readmission rates compared to usual care.

We expect the 1-year event rate to be 47% in the usual care arm based on data obtained on our target population at UPHS. We wish to have 80% power to detect an absolute decrease in this rate of about 10% in the intervention group; this corresponds to a hazard ratio of 0.73. We will accrue 566 patients over the 24-month enrollment period and follow them for an additional 12 months; with the 1:1 randomization ratio, we will have approximately 283 subjects in each arm. The primary hypothesis test will use a two-sided Type I error rate of 0.05. Note that the power calculations are based on the time to first readmission; if patients experience multiple readmissions, statistical power will be increased.

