
### *7.3. Study Duration*

The duration of participation for each individual participant is 12 months from date of enrollment

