## Remote monitoring and behavioral economics in managing patients discharged from the hospital with heart failure: a randomized clinical trial

usual care arm based on data obtained on our target population at UPHS. We wish to have 80% power to detect an absolute decrease in this rate of about 10% in the intervention group; this corresponds to a hazard ratio of 0.73. We will accrue 566 patients over the 24-month enrollment period and follow them for an additional 12 months; with the 1:1 randomization ratio, we will have approximately 283 subjects in each arm. The primary hypothesis test will use a two-sided Type I error rate of 0.05. Note that the power calculations are based on the time to first readmission; if patients experience multiple readmissions, statistical power will be increased. Prior to analysis, we will produce data summaries including graphical methods to assess data quality, examine central tendencies and distributional assumptions and randomization success. The primary analysis will consist of an unadjusted intent-to-treat hypothesis tests using the Andersen-Gill formulation of the Cox proportional hazards model to compare the times to hospitalizations in the two groups; these models properly adjust for the correlation of multiple repeated events within individuals. We will also estimate multivariate regression models adjusted for the stratification variable and other covariates of interest (such as patient sex, income, race, baseline ejection fraction, and quality of life), retaining these given evidence of confounding or predictive ability. We will employ a confounder selection method based on "change in estimate" criterion. We will assess interaction terms between the a priori potential effect modifiers such as income level, race, and baseline ejection fraction. All hypothesis tests will be two-sided and models will be assessed using standard diagnostic techniques. We will use standard approaches to assess the modeling assumptions and include interaction terms with time if necessary. Handling of missing data is an important issue in all RCTs. Follow-up data may be missing if participants miss the follow-up visit or withdraw. Even in subjects who are lost to follow-up, we will be able to capture any events that result in hospitalization, and thus will still be able to observe our primary outcome. This includes hospital discharges from Penn Medicine as well as obtaining state-based discharge data and from Pennsylvania, New Jersey and Delaware to ensure that all readmissions that occur outside of Penn Medicine are captured. In addition, some subjects may receive a heart transplant during the course of the study. Because the disease trajectory and treatment paradigm change significantly with that event, we will censor patients at the time of transplant; the admission to conduct the transplant will count as an event, but follow-up will cease then and patients will be removed from the risk set. We will compare dropout rates by arm, will attempt to find the reasons for missing data and will compare baseline characteristics in participants with complete vs. incomplete follow-up. If enrolled intervention patients receive a heart transplant or ventricular assist device during their 12 month participation they will no longer be eligible to participate in the remote monitoring and their data will be censored from the date they receive the transplant or VAD going forward. An additional secondary endpoint will be cause-specific rehospitalizations, the rationale being that evaluating cause-specific hospital admission will allow a more complete understanding of the potential effects of the intervention, by indicating how many of the readmissions are due to what cause (e.g., heart failure, MI, stroke, other cardiovascular cause, noncardiovascular cause, etc). In secondary analyses we will investigate the sensitivity to modeling assumptions using imputation models and inverse-probability-weighted estimating equations and models that adjust for informative missing data. Patient days spent hospitalized, in rehab or at a SNF will not count towards adherence and will be removed from numerator and denominator and considered unmeasurable for adherence. For the qualitative interviews, the Research Scientist and Clinical Research Coordinators will review all data for recurring themes. As our interest is in the differences and similarities between the groups of patients noted above, we will conduct cross-case analyses to identify the factors that may be associated with patient adherence and readmission. The analysis will consist of describing factors in each of the groups and then comparing those factors across groups.

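### The 80% power claim does not fit 12 months of follow-up per patient: on the SAP's own first-readmission basis 566 patients give about 68%, and the claim that repeat readmissions raise power is not backed by a calculation

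*Supplement*

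**What the plan says.** The Final Statistical Analysis Plan, under Statistical considerations, gives these inputs:

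- Control rate: "We expect the 1-year event rate to be 47% in the usual care arm".
- Target: power of 80%, where the size of the fall is given as "10% in the intervention group; this corresponds to a hazard ratio of 0.73".
- Test level: the primary test "will use a two-sided Type I error rate of 0.05".
- Size and timing: 566 patients, about 283 per arm, accrued "over the 24-month enrollment period and follow them for an additional 12 months".
- Basis: time to first readmission, with the added remark that "if patients experience multiple readmissions, statistical power will be increased".

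Final Study Protocol section 10 repeats this text. Section 7.3 of the same protocol says "The duration of participation for each individual participant is 12 months from date of enrollment", and the primary aim (section 4.1) is the rehospitalization rate over 12 months of enrollment. The primary analysis in both documents is an unadjusted Andersen-Gill model on all readmissions. The summary of analysis plan changes explains the rise from 500 to 566 by a censoring rate that was higher than expected.

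**The concern.** The accrual sentence in the power paragraph reads naturally as follow-up to one closing date, which would give each patient between 12 and 36 months. The rest of the protocol gives each patient 12. First events accumulate with follow-up, so a power figure obtained under the longer schedule does not carry over to the shorter one.

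Two things are at stake. The plan states a power that its design may not have on the basis it names. And the reader is reassured that repeat readmissions will add power, although no rate, rate ratio or overdispersion is given from which this could be checked. The loose wording also leaves unclear which readmissions fall inside the analysis window.

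**Working it through.** **Inputs from the documents.** Control one-year risk 0.47; intervention about 0.37; hazard ratio 0.73; two-sided 0.05; 80% power; 566 patients (500 before the increase), 1:1. Assumed here: constant hazards and, for a common closing date, uniform accrual.

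**The stated hazard ratio.** ln(0.63)/ln(0.53) = 0.728, which rounds to the stated 0.73.

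**Events needed (Schoenfeld).** 4 × (1.960 + 0.8416)² / (ln 0.73)² = 317.

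**Trying to reproduce 80%.** Yearly hazards are −ln(0.53) = 0.635 and 0.73 × 0.635 = 0.463. With follow-up uniform between 12 and 36 months, the chance of a first event is 1 − (e^−λ − e^−3λ)/(2λ), which is 0.700 and 0.590, mean 0.645. Power is Φ(√events × |ln 0.73|/2 − 1.960).

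- 500 patients: 500 × 0.645 = 322 events, power 81%.
- 566 patients, no censoring: 365 events, power 85%.

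So 80% at the base size of 500 is matched under a common closing date.

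**Power with 12 months per patient.** The intervention risk is 1 − e^−0.463 = 0.371, and the mean event probability is (0.47 + 0.371)/2 = 0.420.

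- 566 patients: 566 × 0.420 = 238 events; √238 × 0.3147/2 = 2.427; Φ(2.427 − 1.960) = 68% (69% with the unrounded ratio 0.728).
- 500 patients: 210 events, 63%.
- A comparison of two proportions, 47% vs 37% with 283 per arm, gives 67%.
- 80% power with 566 needs a hazard ratio of about 0.69, that is 47% vs about 35.5%.
- 80% power at 0.73 would need 317/0.420 = about 754 patients (about 740 with 0.728).

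These figures allow for no early censoring. If 11.7% of the information were lost (1 − 500/566, the allowance implied by the increase), power would be about 63%. That is a lower bound for this rate: censored patients contribute time first, and the transplant admission itself counts as an event.

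**Andersen-Gill on all readmissions, 12 months, 283 per arm.** The model is assumed: gamma frailty with variance θ, robust variance of the log rate ratio (1/μ0 + 1/μ1 + 2θ)/283, and μ0 set so that 47% of controls have at least one readmission. Two definitions of the effect are possible.

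| θ | μ0 | Power, rate ratio held at 0.73 | Intervention first-event risk then | Power, first-event risk 47% to 37% | Rate ratio this implies |
|---|---|---|---|---|---|
| 0 | 0.635 | 78% | 37.1% | 79% | 0.73 |
| 0.25 | 0.688 | 76% | 37.7% | 82% | 0.71 |
| 0.5 | 0.747 | 74% | 38.3% | 84% | 0.70 |
| 1 | 0.887 | 69% | 39.3% | 88% | 0.66 |
| 2 | 1.280 | 59% | 41.0% | 94% | 0.59 |

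With the rate ratio fixed, heterogeneity between patients adds the term 2θ, which extra events do not shrink, so power falls. With the absolute first-event effect fixed, the implied rate ratio strengthens as θ grows, so power rises.

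**The case against.** The strongest reply is that the log-rank test on first readmission is no longer the primary analysis. The SAP says openly that its power basis is first readmission and that repeat events come on top. It also defines the effect as an absolute fall of about 10 points, and the hazard ratio is only what that fall corresponds to. Holding the 10-point fall fixed, the Andersen-Gill figures are 79% to 94%, which bears the SAP's remark out. At the 59% end of the other column the first-event risk falls by only 6 points.

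Much of this stands. A reader might infer that the trial has only 68% power for its primary hypothesis, or that it would miss a 10-point reduction one time in three. The documents do not support either reading, because 68% belongs to a first-event test and the primary test uses all readmissions. Nor do they say that the 80% was computed with a common closing date. That is an inference from the wording and from the match at 500 patients, since no calculation is shown.

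The reply does not rescue the stated figure. The 80% is expressly a first-event figure, and with 12 months per patient the plan's own inputs give 68%. If the accrual sentence was meant as 12 months per patient, the 80% is simply unsupported. The favourable Andersen-Gill column also rests on a rate ratio and overdispersion that appear nowhere in the plan.

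**Conclusion.** The power statement is wrong as written. On its own first-readmission basis, with the 12 months that section 7.3 and the primary aim allow, 566 patients give about 238 first readmissions and about 68% power at a hazard ratio of 0.73 before censoring. The effect detectable with 80% power is about 0.69. This rests on the stated inputs and proportional hazards; the two-proportion check gives nearly the same answer.

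The claim that multiple readmissions will raise power is not assured. Compared with 68%, the assumed Andersen-Gill model gives anything from 59% to 94%, depending on the overdispersion and on whether the effect is a rate ratio of 0.73 or a 10-point fall in first-event risk. Neither range is a figure from the documents. The power of the planned primary test is therefore unstated rather than known to be low.

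**What to change.** Keep 566 and amend the wording in the SAP (Statistical considerations) and in protocol section 10:

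- Replace the clause on follow-up after accrual with a statement that each patient is followed for 12 months from enrollment.
- State about 238 expected first readmissions, about 68% power at a hazard ratio of 0.73, and about 0.69 as the ratio detectable with 80% power. Label all three as first-event figures before censoring.
- Replace the sentence on multiple readmissions with an Andersen-Gill power figure for a stated rate ratio, mean readmission rate and overdispersion, and show the range over plausible overdispersion.
- Do not present 68% as the power of the primary Andersen-Gill test.

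The cost is an amendment to the text and one further calculation. No patients, data or analyses change; the stated first-event power becomes less favourable.
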